#### Demographics

A study-specific questionnaire will be used to collect information on participants’ age, gender, country of birth, previous employment, educational background, current health status, and duration of residence at the study-specific RAC facility. These data will be collected at baseline only. Demographic information for the staff will be collected during the focus-group interview, including age, gender, education, and profession.

### Plans to promote participant retention and complete follow-up {18b}

Upon enrollment in the study, the research team will encourage participants to adhere to the intervention and complete the follow-up. However, it must be acknowledged that participants in this research project reside in RAC facilities and are, to some extent, frail. Their health status may deteriorate during the trial, potentially impacting retention rates in both groups. To support participant retention, flexible scheduling of interviews and data collection will be offered, including the option to divide follow-up interviews into shorter sessions to reduce fatigue. In addition, regular check-ups by rehabilitation staff will be provided to both participants and nursing assistants to maintain engagement and identify early signs of withdrawal risk. The research team will also work in close collaboration with RAC staff to facilitate reminders and logistical support. Clear and respectful communication will be emphasized throughout, highlighting the importance of each participant’s contribution to the study.

In the event that a participant discontinues the intervention or withdraws from the study, the research team will request permission to collect available follow-up data, if ethically and practically feasible. When provided, the reason for withdrawal will be documented. All data collected up to the point of withdrawal will be included in the final analysis, in accordance with the intention-to-treat principle.

### Data management {19}

A data management plan (DMP) has been created to describe how the research data will be collected, stored, handled, documented, used, and made available during and after the research project. The DMP can be obtained from the researchers upon request.

In summary, participants will be registered immediately after inclusion in the eCRF system (GGC) using their unique study IDs. During the assessments, all data will be entered into the GGC system by the non-blinded researcher. All paper forms will be labeled with the study ID and securely stored in accordance with local data management arrangements. Personally identifiable paper records, such as informed consent forms, will be stored separately from anonymized paper records.

Once data collection is complete, the database in GGC will be locked and exported to secure, encrypted, and backed-up servers. Any modifications to the raw data, as well as, all steps involved in the analysis, will be thoroughly documented. The storage of personal information and registration will comply with the European Union (EU) General Data Protection Regulation (GDPR).

All data will be retained for at least 17 years.

### Confidentiality {27}

In addition to what is described in the previous section regarding data management, only the research group will have access to the data during the data collection, analysis, and publication phases. An external statistician will have access to the data during the analysis phase. Personal ID numbers for the included participants will be delivered in encrypted form to the authorities responsible for medical records and administrative systems included in the study.

### Plans for collection, laboratory evaluation, and storage of biological specimens for genetic or molecular analysis in this trial/future use {33}

Not applicable, as no such collection will occur.

## Analyses

### Statistical methods for primary and secondary outcomes {20a}

Descriptive data will be presented as the mean and standard deviation (SD) or median and interquartile range (IQR) for numeric variables, as appropriate. Categorical variables will be presented as numbers and percentages. Baseline characteristics will be described by randomization group.

Efficacy analyses will be conducted according to the intention-to-treat (ITT) principle, analyzing participants according to their original randomization assignment. Primary and secondary outcomes will be compared between groups using analysis of covariance (ANCOVA), adjusted for baseline values, and study center. All instrument scales (e.g., COPM, EQ-5D-5L, WHO-5) will be treated as continuous variables in the analyses. Robust standard errors (using the HC3 method) will be employed to ensure valid inferences in the presence of deviations from normality. Results will be presented as adjusted mean differences between groups, with corresponding 95% confidence intervals (CIs). The number and proportion of participants showing improvements of more than 1, 2, or 3 units will also be presented descriptively and compared between groups. The level of physical activity will be classified as sedentary, light intensity, or moderate to vigorous as per Hansen et al. and Forster et al. [55, 56].

All tests will be two-tailed and conducted at a 5% significance level. Missing data will be handled using multiple imputation. Statistical analyses will be performed using SAS/STAT® Software, Version 9.4 or later (SAS Institute Inc., Cary, NC, USA) and IBM SPSS Statistics 26 or later (IBM Corp., Armonk, NY, USA).

### Analysis of qualitative data

The individual semi-structured interviews will be analyzed using qualitative thematic analysis [29].

The analysis process will follow six steps [57]. Step 1 begins with familiarization with the material by reading and listening to the interview data. In Step 2, codes will be generated, followed by Step 3, in which the search for themes will begin. In Step 4, the themes will be reviewed, and in Step 5, they will be finalized and named. Finally, in Step 6, the manuscript will be written.

In the focus-group interviews with nursing staff, data will be analyzed using the methods described by Krueger and Casey [30] and Dahlin-Ivanoff and Holmgren [31]. The analysis will generate categories that reflect the discussions of the focus group participants relevant to the purpose of the project, emphasizing the meaning derived from the collective discussions rather than individual comments [30].

To strengthen the credibility of the analysis process, all researchers involved in the project will to some degree participate in the analysis. The process will continue until consensus is reached among the researchers.

All data will be analyzed using NVivo (QSR International, Inc., Cambridge, MA, USA) qualitative data analysis software.

### Health-economic analysis

A cost–utility analysis using individual data will be performed from a healthcare perspective [58]. Cost-effectiveness ratios will be based on the changes in QALY and net costs for the intervention group compared with the control group. Results will be presented as an incremental cost-effectiveness ratio (ICER), expressed as ICER = Ca − Cb/Ea − Eb, where Ca and Cb represent the costs for the intervention and control groups, respectively, and Ea and Eb represent the QALY changes for the intervention and control groups, respectively. Sensitivity analyses will be conducted to account for uncertainty in parameter estimates by incorporating both British [59] and Swedish [60] value sets for the health state preferences, as well as varying costing approaches.

QALYs will be derived from the EQ-5D-5L [44–46] using the summary index score based on societal preference weights (“utilities”). The health state index scores range from less than 0 (a health state equivalent to dead, with negative values representing values worse than dead) to 1 (the value of full health). Health state preferences typically represent national or regional values and can therefore vary among countries or regions. In this study, both the widely used British value set [59] and the recently developed Swedish value set [60] will be applied.

### Interim analyses {21b}

No interim analysis will be performed.

### Methods for additional analyses (e.g., subgroup analyses) {20b}

There are no predefined subgroup analyses. Exploratory analyses, including subgroup analyses and interaction analyses, may be performed at a later stage. All significant findings from these exploratory analyses will be considered hypothesis-generating and will require confirmation in future studies.

### Methods in analysis to handle protocol non-adherence and any statistical methods to handle missing data {20c}

Protocol non-adherence will be managed according to the ITT principle, analyzing all randomized participants according to their original randomization assignment, regardless of withdrawal, protocol deviations, or noncompliance. Missing values within each instrument will be handled according to the instructions provided in the respective instrument manuals, if available. Other missing data will be addressed using multiple imputation by chained equations.

### Plans to give access to the full protocol, participant-level data, and statistical code {31c}

The datasets generated and/or analyzed during the current study will not be made publicly available due current Swedish ethical legislation and the EU GDPR. However, data may be available from the PI on reasonable request, provided that appropriate permissions are obtained from the relevant authorities.

## Oversight and monitoring

### Composition of the coordination center and trial steering committee {5d}

This research project originates from collaboration among Region Örebro County, Örebro Municipality, and Örebro University, with the aim of increasing the research engagement in the municipality. The project is coordinated by a research group established at the University Health Care Research Center within Region Örebro County. The research group, which also includes researchers from Kristianstad and Mälardalen universities, has ultimate responsibility for the trial, trial design, and adherence to the study protocol.

The PI will ensure that the trial is conducted in line with good clinical practice, oversee the trial, manage trial registration, oversee the DMP, and ensure overall quality. One member of the research group will coordinate communication with the municipality, management, and RAC facilities, and will also be responsible for the intervention, including training and maintaining contact with the staff. Another research group member will be responsible for the HEAP, while an external statistician will be responsible for the statistical analysis plan (SAP). The research team will meet monthly.

A formal Trial Steering Committee (TSC) will not be established. However, strategic oversight and major decisions will be reviewed and approved by a steering group formed through the collaboration among Region Örebro County, Örebro Municipality, and Örebro University (The Collaboration Forum for older adults, Forum 2.0), in addition to the regular meetings of the core research group. The progress of the research project is reported to this steering group (Forum 2.0) every 2 years. During these meetings, independent researchers review the study’s progress to ensure it is proceeding as planned.

### Composition of the data monitoring committee, its role and reporting structure {21a}

The steering group formed through the collaboration among Region Örebro County, Örebro Municipality, and Örebro University (The Collaboration Forum for older adults, Forum 2.0) will also maintain overall oversight of the project as no formal Data Monitoring Committee (DMC) will be established. Additionally, Region Örebro County will be responsible for addressing data safety and quality issues, and for safeguarding the interests of the study participants.

### Adverse event reporting and harms {22}

AEs are defined as; any untoward medical occurrence in a study participant, regardless of its relationship to the intervention. A serious AE (SAE) are defined as an AE that results in death, is life-threatening, requires inpatient hospitalization or prolongation of existing hospitalization, or results in persistent or significant disability or incapacity.

Any AE or harms resulting from study participation will be reported and managed by the on-site clinical staff or the research team, depending on the nature of the event. Management will follow standard clinical care procedures.

AEs will be collected throughout the study period using both unsolicited reporting (initiated by participant or staff) and solicited reporting through direct questioning during follow-up interviews and other participant interactions.

All AEs and SAEs will be documented in the medical records and recorded using a standardized e-CRF to ensure consistent assessment of severity, based on predefined criteria outlined in the Common Terminology Criteria for Adverse Events (CTCAE). Collected data will include onset, duration, severity, relationship to the intervention, expectedness, and outcome. Events will be evaluated by unblinded research staff in collaboration with healthcare professionals.

Severity will be graded on a scale from 1 to 5 (mild, moderate, severe, life-threatening, and death). Each AE will also be assessed for its likelihood of being related to the intervention, and whether it is expected or unexpected based on known or anticipated risks, including differences in nature, severity, or frequency.

SAEs will be reported to the PI within 24 h of becoming known. Non-serious AEs will be documented and reviewed during regular project meetings and included in interim reports. If required, external reporting to oversight bodies (e.g., ethics committee or sponsor) will be conducted in accordance with national and institutional guidelines.

Participants experiencing AEs will be referred to their usual healthcare providers. All AEs will be monitored until resolution or stabilization.

Potential unintended effects related to the trial process itself (e.g., stress from assessments or burden from participation) will be monitored thorough participant feedback, staff reports, and observed behavior. Any such findings will be reviewed and addressed by the core research team in collaboration with the responsible rehabilitation staff.

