In Sweden, reablement interventions in RAC facilities have not previously been studied. To address this gap, our research group has developed a reablement intervention tailored to the Swedish context, referred to as Reablement in Residential Aged Care (Re-RAC). A feasibility study was conducted to assess the intervention and study procedures, demonstrating their practicality and applicability [28]. The evaluation revealed no significant harms, which was anticipated given that the program is designed to enhance functional ability through use of low-intensity, individualized activities adapted to each participant’s capacity. Nonetheless, potential risks that may include temporary fatigue, frustration, or reduced motivation require continued investigation and evaluation on a larger scale. Thus, further evaluation is necessary through a larger-scale study using a randomized controlled trial (RCT) design to establish its efficacy and generalizability.

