### Additional consent provisions for collection and use of participant data and biological specimens {26b}

Data on healthcare consumption, pharmaceutical prescriptions, adverse events (AE), and adherence to the intervention will be extracted from medical records and healthcare administration systems. In the consent form, participants will be requested to allow the extraction of such data.

This study does not involve the collection and storage of biological samples.

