##### Preparatory training and support for staff before and during intervention

Before the start of the study, all staff at the included wards will participate in a half-day (3.5-h) training session covering both theory and practice. Topics will include reablement, gerontology, motivational strategies, and teamwork. Case scenarios based on person-centeredness, healthy aging, and previous research on reablement will be presented and discussed in smaller groups. The training will also provide information about the practical implementation of Re-RAC, including motivational strategies and empathetic engagement. A film featuring a voluntary participant in the feasibility study [28] will be used to illustrate the process, from the initial interview to the implementation of the goal-oriented support plan and teamwork, further clarifying the Re-RAC working method.

The rehabilitation staff at each participating RAC facility will also participate in an additional half-day (3.5-h) training session specifically focused on helping nursing assistants in the implementation of the support plan and conducting check-ups. Check-ups will be offered in weeks 3 and 6 by the OT to provide support to both the participants and the nursing assistants. These check-ups are intended to identify any necessary adjustments to the intervention’s content and to provide ongoing support to both the participant and the nursing assistants as they work through Re-RAC. An additional purpose of these check-ups is to help the nursing assistants maintain the participants’ motivation and engagement throughout the process.

During the intervention, regular team meetings (involving nursing assistants, nurses, and the OT) held every other week and ward meetings (including all ward staff and the ward manager) held every fourth week will be used to communicate information about the intervention and the specific activities for each participant. These forums will also provide opportunities for reflection and guidance among the staff. Additionally, the OT will offer individual oral and/or practical guidance to the nursing assistants as needed.

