A goal-oriented support plan with specific activities to achieve the goal is developed by the OT together with the participant. A nursing assistant such as the participant’s contact person at the RAC can also be involved depending on the needs of the participant. These activities may include the use of assistive devices, environmental adjustments, and modified activity behaviors, such as physical exercise or task-specific training. Multiple training activities may be included and are tailored to the individual’s daily capacity. The time allocated for each participant is customized based on their needs and the nature of the goal. The intensity of the intervention can range from 2 to 7 days per week, with training sessions occurring once or multiple times per day, and each session lasting up to a maximum of 30 min.

The intervention lasts 8 weeks. The OT introduces the nursing assistants, who will support the older adult during the intervention, to the person-centered goal and the planned activities in the support plan. The nursing assistants receive supervision on how to support the specific participant according to the previously described support plan for staff. The intervention aims for ongoing progress with an increasing level of difficulty. Thus, the nursing assistants can adjust the level of difficulty based on the participant’s progress in their occupational performance. Additionally, the OT, PT, or the participants can initiate adjustments to improve the performance.

After 8 weeks, the intervention concludes with a renewed COPM assessment [42, 43], during which the participant’s occupational performance and satisfaction with the performance, related to the person-centered goal, are evaluated.

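### Adverse events are solicited at undefined contacts that are far more frequent under Re-RAC, so by-arm counts of mild events are open to ascertainment bias against Re-RAC

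*Protocol article*

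**What the plan says.** Adverse event reporting and harms {22} sets two collection routes for the whole study period: unsolicited reports from participants or staff, and "solicited reporting through direct questioning during follow-up interviews and other participant interactions". It does not say what counts as an interaction beyond the follow-up interviews, who asks, or at which time points. Table 1 has no adverse-event row. Events are graded 1 to 5 by CTCAE, serious events are defined separately, and evaluation is by unblinded research staff.

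A third route appears under Additional consent provisions {26b}: "Data on healthcare consumption, pharmaceutical prescriptions, adverse events (AE), and adherence to the intervention will be extracted from medical records" and administrative systems. No period is given there. Table 1 places record extraction at w−12 to w0 and w9 to w20, and Plans for assessment and collection of outcomes {18a} gives matching windows of 3 months before baseline and 3 months after the intervention.

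Contact differs by arm. For Re-RAC, Implementation of the intervention states "The intervention lasts 8 weeks" and "The intensity of the intervention can range from 2 to 7 days per week". The section on staff training and support adds: "Check-ups will be offered in weeks 3 and 6 by the OT". Participant experiences plans later interviews with 15 to 18 Re-RAC participants only. Controls receive usual care without active support toward their goal ({6b}, {11d}), and Table 1 shows no assessment for either arm between w0 and w9.

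Harms are part of the rationale. Background and rationale {6a} says that "potential risks that may include temporary fatigue, frustration, or reduced motivation require continued investigation and evaluation on a larger scale".

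**The concern.** When solicited enquiry is tied to contact, the chance of recording an event depends on how often a participant is seen. Here the intervention itself sets that frequency, so events that occur equally often can be counted unequally. The risks named in the background are transient and subjective, and such events depend most on someone asking soon after they occur.

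A published table of adverse events by arm could then show more mild events under Re-RAC with no true excess. A true excess could not be told apart from closer observation. An analysis plan cannot repair this afterwards, because it cannot restore events that nobody asked about in one arm.

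**Working it through.** The plan states no figure on this point, so there is none to reproduce. The check has three steps.

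**1. Trial-specific contacts in weeks 1 to 8**

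- Re-RAC training days: 2 × 8 = 16 to 7 × 8 = 56.
- Re-RAC OT check-ups: 2 (weeks 3 and 6).
- Re-RAC total: 16 + 2 = 18 to 56 + 2 = 58, or more where there are several sessions a day.
- Control: none stated.
- Common to both arms: baseline and week 9.

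The retention section {18b} mentions check-ups without naming an arm. Read with the staff-support section and {11c}, they belong to the intervention.

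**2. Period covered by records**

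The stated windows end at w0 and resume at w9. Weeks 1 to 8, when harms of the intervention would arise, lie between them. The gap may be one of wording: {18a} lists adherence among the data drawn in these windows, yet adherence arises during the intervention, and {26b} names adverse events without a period. As written, though, nothing assures equal record coverage of weeks 1 to 8. The {22} statement that events are documented in the medical records helps only once an event has been noticed.

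**3. Illustration of size, with equal true risk in both arms**

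Let b be the share of events captured by routes common to both arms (unsolicited reports, records, week-9 questioning). Let k be the number of extra solicited contacts in Re-RAC, and q the chance that one such contact picks up an event otherwise missed. Contacts are treated as independent. Then:

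- control reported risk = true risk × b
- Re-RAC reported risk = true risk × [1 − (1 − b)(1 − q)^k]
- apparent risk ratio = [1 − (1 − b)(1 − q)^k] / b, in which the true risk cancels.

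Example with b = 0.7, q = 0.3, k = 2: [1 − 0.3 × 0.49] / 0.7 = 0.853 / 0.7 = 1.22. At an assumed true risk of 30%, that is 21.0% reported in controls and 25.6% in Re-RAC.

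| Extra solicited contacts | b = 0.5 | b = 0.7 | b = 0.9 | b = 1.0 |
|---|---|---|---|---|
| k = 2, q = 0.1 | 1.19 | 1.08 | 1.02 | 1.00 |
| k = 2, q = 0.3 | 1.51 | 1.22 | 1.06 | 1.00 |
| k = 2, q = 0.5 | 1.75 | 1.32 | 1.08 | 1.00 |
| k = 18, q = 0.1 | 1.85 | 1.36 | 1.09 | 1.00 |

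The first three rows suppose that only the two check-ups add questioning. The last supposes that training days do so as well, which the protocol does not say. Both b and q are assumptions; the document gives neither.

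**The case against.** The strongest reply is that the protocol does not prescribe unequal questioning. Several parts of it stand.

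- A reader might infer that adverse events are asked about at every contact, training sessions included. The text does not say so. The logbook fields under Health-economic parameters are date, activity, time spent and profession, with none for adverse events. The 16 to 56 training days are opportunities for enquiry, not counted enquiries.
- A reader might infer that a planned between-arm test of harms is biased. No such test is specified: {20a} compares primary and secondary outcomes, adverse events are not among them, and harms are not in Objectives {7}. The concern applies to any tabulation by arm.
- Shared routes exist. Unsolicited reports are open to both arms, staff are present around the clock, and participants of both arms may live on the same ward. One could assume that controls are detected only by recall at week 9, with 30 to 50% capture against 80 to 90% under Re-RAC, and so reach ratios of 0.8/0.5 = 1.6 to 0.9/0.3 = 3.0. Those rates are invented and leave out the shared routes.
- Serious events can be separated from mild ones with the planned SAE definition and CTCAE grades, so admissions and deaths need not be blurred by mild events.

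What the reply does not remove is that solicitation rests on undefined contacts, that the scheduled contacts differ sharply by arm, and that the stated record windows miss the intervention period.

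**Conclusion.** The point holds in limited form. By-arm counts of mild, non-serious events are open to ascertainment bias against Re-RAC. The direction follows from the design if the extra Re-RAC contacts prompt any enquiry and the shared routes are incomplete.

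The size is unknown. With two check-ups as the only extra enquiry, equal true risk gives an apparent risk ratio of about 1.0 to 1.75 for assumed shared capture of 100% down to 50%. The effect vanishes for events that the shared routes capture fully, so deaths and hospital admissions should be little affected.

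A reader might go further and conclude that the trial cannot weigh benefit against risk. The documents do not support that: serious events remain comparable, and weighing risk is part of the background rationale, not a stated objective. This is a cheap and worthwhile improvement, not a defect in the efficacy comparison.

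**What to change.** In {22}, base between-arm reporting of adverse events on sources that are equal in both arms:

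1. The same adverse-event questions at the same time points in both arms, at least at week 9, with a fixed recall period.
2. Falls, admissions, deaths and other recorded events from medical records over the same period from allocation, explicitly including weeks 1 to 8. Align Table 1 and {18a} with this.
3. A field in the e-CRF for the source of each event. Events detected only at Re-RAC sessions, check-ups or interviews are reported separately, as a description of that arm.

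Define the other interactions at which questions are asked, and leave SAE reporting unchanged.

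The cost is protocol and e-CRF wording plus a longer record extraction. {26b} already asks consent to extract adverse-event data, but whether the consent form limits the period should be checked. Mild events seen only at sessions leave the between-arm comparison, and recall at week 9 will miss some transient events in both arms. Recruitment began in October 2024, so participants already followed up will lack the common questions; their record data for weeks 1 to 8 may still be obtainable.
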